### Withdrawal, Dropout, and Discontinuation

Patients have the right to exit the study at any time. Dropouts and reasons for leaving will be documented in the case report form (CRF). Data on these participants will also be incorporated into the statistical analysis. The reasons for discontinuing the trial by the principal investigator are: (1) participant experiences more clinical complications or a serious adverse event; (2) financial and management reasons; (3) administrative authorities terminate the trial.

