### Sample Size Calculation

The sample size was estimated using hs-CRP. Currently, the hs-CRP of NSTEACS decreased from 5.30 mg/L to 3.74 mg/L after 14 days of conventional treatment, with a decline rate of 29.43% (26). The hypothesis is that the treatment group could reduce the hs-CRP of NSTEACS by 35%. With a type I error rate of α = 0.05 and a power of 80% (a type II error rate of β = 0.2), one arm requires a sample size of 27. With a 20% drop-out rate, we have to recruit a total of 66 patients. The following is the formula for calculating sample size (27):

$$\begin{array}{l} \text{n}=2{\left[\frac{\left({\text{u}}_{\alpha }+{\text{u}}_{\beta }\right)}{\delta /\sigma }\right]}^{2}+\frac{1}{4}u_{\alpha }^{2} \end{array}$$

n, is the sample size required in each group, δ = μ_1_-μ_2_, is the difference between means of two groups, σ, is the standard deviation, u_α_ and u_β_ are the values of u corresponding to the test level α and type II error probability β, respectively.

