### Statistical Analyses

An independent biostatistician will perform statistical analysis. The result of recruitment, the specific reasons for data missing and the distribution of each statistical analysis data set will be described. The primary outcome, the change values of hs-CRP from recruitment to day 7 ± 3, day 14 ± 3 and the day of revascularization, and the secondary outcome, the change scores in five dimensions of SAQ at the same time, are both continuous variables. For comparison between groups, the continuous variables will be described using means ± SD, median, interquartile range, etc., and the Shapiro-Wilk normality test and Levene test for variance homogeneity will be performed. A Student *t* test will be used to compare two groups that have a normal distribution with homogeneous variance, otherwise the Wilcoxon rank-sum test will be used. When some continuous variables are converted into categorical variables, these categorical variables will be described using rates, and the chi-square test or Fisher's exact probability method will be used. For comparison within groups, the paired *t* test or Wilcoxon signed-rank test will be used for continuous variables and the McNemar test for categorical variables. If there are baseline imbalances, Cox regression analysis, logistic regression and multivariate analysis of covariance will be used to adjust confounding variables. The longitudinal data with repeated measures will be analyzed using the linear mixed-effects model to assess associations. The safety analysis will tabulate a detailed description of the adverse reactions, adverse events and serious adverse events and compare the difference in incidence between two groups using Fisher's exact probability method. A difference of *P* < 0.05 at two-tailed test will be considered statistically significant in all analyses. The statistical analyses will be performed using SAS software version 9.4 (SAS Institute, Cary, NC, USA).

After metagenomic sequencing is completed, microbiota community structures will be compared at different taxonomic levels. The abundance and diversity of intestinal flora will be analyzed. The relationship between microbiota composition and clinical outcomes will be investigated using univariate and multivariate linear and nonlinear mixed and regression models. Gene annotation will be conducted to study the function of the intestinal flora.

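### At day 14 the t or Wilcoxon test on hs-CRP change leaves out participants without a day-14 value; the mixed model already planned should be the primary analysis

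*Protocol article*

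**What the plan says.** Four statements in the protocol article bear on this.

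- **Withdrawal, Dropout, and Discontinuation**, on those who leave: "Data on these participants will also be incorporated into the statistical analysis". No method is attached.
- **Statistical Analyses**, on the outcome: "The primary outcome, the change values of hs-CRP from recruitment to day 7 ± 3, day 14 ± 3 and the day of revascularization". On the comparison between arms: "A Student *t* test will be used to compare two groups that have a normal distribution with homogeneous variance", and "otherwise the Wilcoxon rank-sum test will be used". Adjustment by regression or covariance methods is mentioned only for the case that baseline imbalances appear.
- **Statistical Analyses**, further on: "The longitudinal data with repeated measures will be analyzed using the linear mixed-effects model to assess associations". Neither the outcome nor the rank of this model, primary or supportive, is given. The section also promises that "the specific reasons for data missing and the distribution of each statistical analysis data set will be described".
- **Sample Size Calculation**: 27 per arm are required, and "With a 20% drop-out rate" the total becomes 66.

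Outcomes Measures and Table 1 schedule hs-CRP at baseline, day 7 ± 3 and day 14 ± 3.

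**The concern.** A two-sample test on change needs both the baseline value and the value at the visit in question. Someone who leaves before day 14 has no day-14 change and cannot enter that test unless a value is supplied. The one named method that can use an incomplete series, the linear mixed-effects model, is not tied to the primary comparison. Read as written, the day-14 result can therefore rest on those who stayed, although the article says that dropouts' data are used.

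What is at stake is bias. In this population departure may be related to outcome. The article lists clinical complications and serious adverse events among the reasons for discontinuation, and its Introduction links hs-CRP to inflammation in acute coronary syndrome and to later events. That leavers would differ in hs-CRP change is an inference from these statements; no figure in the article shows it. The planned difference is small, so even a modest distortion would be visible against it.

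A second, smaller loss is precision: a test on raw change does not use baseline hs-CRP as a covariate.

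**Working it through.** **1. The plan's own numbers.** Inputs from Sample Size Calculation: 27 per arm, 20% dropout, total 66.

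- 27 × 1.20 = 32.4, rounded up to 33 per arm, 66 in total. This reproduces the stated figure.
- 27 / 0.80 = 33.75, rounded up to 34 per arm, 68 in total. This is within two patients of it.

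**2. Who is in the day-14 test at the planned loss.**

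- With a day-14 value: 66 × 0.80 = 52.8, or 33 × 0.80 = 26.4 per arm.
- Without: 66 × 0.20 = 13.2.

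Some of these 13 may have a Visit 2 value; the article does not say how many to expect. Those who do enter the day-7 test.

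**3. Is power the problem?** No. The article gives no standard deviation, so the standardised difference has to be solved from its formula with n = 27, two-sided α = 0.05 and 80% power:

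- u_α²/4 = 1.96²/4 = 0.96
- (27 − 0.96)/2 = 13.02, square root 3.61
- δ/σ = (1.96 + 0.84)/3.61 = 0.776

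At that effect, by normal approximation, power is about 88% with 33 per arm analysed and about 80.5% with 26.4 per arm. Solved one-sided, the effect is 0.685, and the corresponding powers are about 87% and 80%. The inflation already pays for the missing day-14 values.

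**4. Possible bias, under assumptions.** Let p be the proportion lost in an arm and g the mean change in leavers minus that in completers, the same in both arms. The mean over all randomised in an arm is the completer mean plus p × g. The completer contrast is therefore off by (p₁ − p₂) × g in size.

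The planned difference is 5.30 × (0.35 − 0.2943) = 0.295 mg/L. This assumes that both arms start at 5.30 mg/L, the control figure in Sample Size Calculation.

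| Assumed loss | g = 0.5 mg/L | g = 1 mg/L | g = 2 mg/L |
|---|---|---|---|
| 20% and 20% | 0 | 0 | 0 |
| 20% and 10% | 0.05 (17%) | 0.10 (34%) | 0.20 (68%) |
| 30% and 10% | 0.10 (34%) | 0.20 (68%) | 0.40 (136%) |

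Entries are mg/L, with the percentage of 0.295 in brackets. The split between arms and every value of g are assumptions. The 20%/10% row averages 15% loss; the 30%/10% row averages the stated 20%. The top gap of 2 mg/L exceeds the whole expected control-arm fall of 5.30 − 3.74 = 1.56 mg/L, so the right-hand column is an extreme.

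**5. Precision.** If the variance is equal at the two times and the correlation between them is ρ, the variance of the baseline-adjusted contrast relative to the change-score contrast is (1 + ρ)/2, which is never above 1. The article gives no ρ, so the gain cannot be sized.

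**The case against.** A reader might infer that the article contradicts itself and that its primary analysis is a completers' analysis. The text does not carry that far.

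- The statement on dropouts can mean data collected up to exit. It does not say that every dropout enters every test.
- Dropouts' data have several routes into the analysis: the day-7 comparison, the mixed model and the safety tables. Nothing excludes the mixed model from hs-CRP, which is measured repeatedly.
- No completer or per-protocol set is named as primary. More than one analysis set is foreseen. Definitions of sets and imputation rules are commonly left to the analysis plan or full protocol, which are not shown, so their absence is no fault here.
- Inflating for 20% loss is routine and commits the plan to no particular analysis set.

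All of this stands, and it removes the charge of contradiction.

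Two further objections bear on the remedy. A mixed model is valid when missingness depends on observed values; if leavers differ in ways not recorded, bias remains. And if baseline enters only as a covariate, a participant with nothing but a baseline value adds nothing to the contrast. Both are correct and shape the fix.

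What the objections do not remove is that the test named for comparing the arms omits, at day 14, anyone without that value, while a method that keeps partial records is already in the plan without a stated primary role.

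**Conclusion.** The point holds in a limited form. For the day-14 contrast, the named t or Wilcoxon test does not by itself deliver the statement that dropouts' data are used, and it makes no use of baseline as a covariate. The role of the mixed model in the primary comparison is open. About 13 of 66 participants would be outside the day-14 test at the planned loss; power stays near 80%.

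The bias cannot be sized from the documents. With loss of 20% against 10% and a gap of 0.5 to 2 mg/L, it is 0.05 to 0.2 mg/L, or 17% to 68% of a planned 0.295 mg/L that itself assumes a common baseline of 5.30 mg/L. With equal loss and equal gaps it is zero. It would be wrong to read the 68% as an expected bias, or to conclude that the randomised comparison is lost: both need more than the article says.

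The change is worth making because it replaces the stated test with a better one from the same section.

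**What to change.** In Statistical Analyses, name the linear mixed-effects model as the primary analysis of hs-CRP, with arm, visit and arm-by-visit as fixed effects, and take the day-14 contrast between arms as the primary estimate. Fix one of two ways of using baseline hs-CRP:

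- as a covariate, with all randomised participants who have at least one post-baseline value; or
- as a response with a common baseline mean in both arms, with all randomised participants who have any hs-CRP value.

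Analyse on the log scale if hs-CRP is skewed, and settle that before unblinding. Keep the t or Wilcoxon test on observed day-14 change as a sensitivity analysis. State that the model lessens bias when missingness depends on observed values and does not remove bias from data missing not at random.

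The cost is wording. The model is already planned, the three hs-CRP measurements are already scheduled, and Trial Status reports that no analysis has yet been done, so the choice can still be fixed without sight of results.

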### Intervention

All participants will be randomly allocated to one of the following two groups. Participants in the SQSX group will receive conventional treatment plus SQSX, while the placebo group will receive conventional treatment plus placebo, both for 14 days. The conventional treatment is based on the NSTEACS guideline issued by the European Heart Association in 2015 (22), including but not limited to the following: (1) anti-myocardial ischemic drugs: isosorbide mononitrate 20mg twice daily; (2) platelet inhibition: aspirin 100 mg once daily and ticagrelor 90 mg twice daily; (3) anticoagulation: enoxaparin 1 mg/kg s.c. twice daily; (4) invasive coronary angiography and revascularization according to the practical condition; (5) high-intensity statin therapy: atorvastatin 40 mg po qn. The composition and daily dosage of SQSX equal to Huangqi (Astragali Radix) 50 g, Danggui (Angelicae Sinensis Radix) 10 g, Danshen (Salviae Miltiorrhizae Radix Et Rhizoma) 30 g, Ezhu (Curcumae Rhizoma) 20 g, Huanglian (Coptidis Rhizoma) 10 g and Baizhu (Atractylodis Macrocephalae Rhizoma) 10 g. The placebo is made up of 5% granule and 95% dextrin with a look, smell and taste similar to active granule. Both SQSX and placebo (both 10 g per bag) are produced by Beijing Kangrentang Pharmaceutical Co., Ltd. (Beijing, China) in full accordance with the standards of Chinese Pharmacopeia and Good Manufacturing Practice. They use the same package with the study name and drug number printed on the surface. Subjects will be told to mix the granules with 100 mL of boiled water until dissolved and to drink it 30 min after breakfast and dinner. (10 g at a time, twice a day). To ensure adherence, study medicine will be distributed and/or retrieved at each visit.

During the study period, the use of any other Chinese medicine for the treatment of CAD is forbidden. Antibacterial drugs, probiotic drugs, proton pump inhibitors, immunosuppressants, hormones, drugs for gastrointestinal diseases, and drugs with a direct effect on intestinal flora are not permitted.

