### Exclusion Criteria

Any of the single conditions as follows would be excluded: (1) indication for renal insufficiency, blood serum creatinine (Scr) > 220μmol/l in males or Scr > 175 μmol/l in females; (2) significant abnormalities in liver function with alanine transaminase (ALT) and aspartate transaminase (AST) are 3 times above the upper bound of normal; (3) systolic pressure > 160 mmHg or diastolic pressure > 100 mmHg after controlled; (4) diabetic patients with random blood glucose ≥ 13.7 mmol/l or glycosylated hemoglobin ≥ 9.5%; (5) Women who are pregnant, breast-feeding or preparing to be pregnant; (6) combined with acute cerebrovascular disease,severe hematopoietic diseases, psychiatric disorder, or malignant tumor; (7) intestinal disease with inflammation or malabsorption; (8) participated in other clinical trials within 3 months; (9) GRACE score > 140 points (high risk group with 1~3% in-hospital death rate) (24); (10) had received antibiotics, steroids, laxatives, antidiarrheals or probiotics within the preceding 3 months.

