## Discussion

Based on our previous pharmaceutical studies, SQSX shows a good pharmacological effect of neovascularization and preventing in-stent restenosis. In clinical practice, it's also widely prescribed as a complementary medicine for CAD. Therefore, we would like to initiate a randomized, double-blind, placebo-controlled trial to examine the efficacy and safety of SQSX for NSTEACS. ACS is usually accompanied by gastrointestinal ulcers or bleeding (28, 29), and long-term use of antiplatelet drugs or combined use of multiple anticoagulant drugs causes gastrointestinal mucosal damage (30, 31). These pathological states of the intestinal mucosal barrier cause translocation and disturbance of intestinal flora (32). The disturbed intestinal flora and its metabolite TMAO are one of the reasons that promote the progression of CAD (12, 33, 34). As is well known, NSTEACS is at a critical stage from stable to unstable, which is likely to be accompanied by significant changes in the intestinal flora. We consider that SQSX could be an effective intestinal flora regulator, helping to ease the short-term symptoms of NSTEACS by improving intestinal flora disturbances and gastrointestinal tract injury. The study is possible to provide evidence for the use of intestinal flora modifiers in the treatment of ACS. The above hypotheses are still unclear, so we intend to verify in this trial.

There are three limitations to this work. First, the sample size of the study is small and might be biased. Therefore, two subsequent clinical studies with a larger sample size (*n* = 120) will be launched this year as a follow-up supplement. Second, the biomarker hs-CRP is observed as a surrogate indicator for the incidence of MACCE and does not yet fully explain the efficacy. We'll determine whether or not to investigate the incidence of MACCE further according to the result. Third, we only control the effects of combined medications on the intestinal flora, and could hardly standardize the patient's eating habits and other multivariate factors that affect intestinal flora. We will educate patients and document their dietary and lifestyle habits to ensure consistency of multiple factors as much as possible.

To conclude, the purpose of the trial is to examine the efficacy and safety of SQSX for NSTEACS and explore the possible pharmacological mechanisms.

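### The concomitant-drug rule bars proton pump inhibitors, gastrointestinal drugs and antibacterials with no exception for clinical need, in patients treated with aspirin, ticagrelor and enoxaparin

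*Protocol article*

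**What the plan says.** All of the following is from the protocol article.

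- **Background treatment (Intervention).** The conventional regimen includes "platelet inhibition: aspirin 100 mg once daily and ticagrelor 90 mg twice daily" and "anticoagulation: enoxaparin 1 mg/kg s.c. twice daily".
- **Prohibited drugs (Intervention, last sentence).** The list opens with "Antibacterial drugs, probiotic drugs, proton pump inhibitors" and ends with the statement that "proton pump inhibitors, immunosuppressants, hormones, drugs for gastrointestinal diseases, and drugs with a direct effect on intestinal flora are not permitted". It carries no qualifier.
- **Eligibility (Exclusion Criteria).** Criterion 10 removes patients who "had received antibiotics, steroids, laxatives, antidiarrheals or probiotics within the preceding 3 months"; proton pump inhibitors are not on that list. Criterion 7 covers inflammatory or malabsorptive intestinal disease, not gastric ulcer, earlier gastrointestinal bleeding or bleeding risk.
- **Gastrointestinal risk (Discussion).** The authors write that "ACS is usually accompanied by gastrointestinal ulcers or bleeding".
- **Purpose (Discussion, third limitation).** The reason given for the drug limits is the flora: "we only control the effects of combined medications on the intestinal flora".
- **Leaving the trial (Withdrawal, Dropout, and Discontinuation).** One reason for discontinuation is that the "participant experiences more clinical complications or a serious adverse event". Patients may also leave at any time, and the data of those who leave still enter the analysis.

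**The concern.** The background regimen combines two antiplatelet drugs with an anticoagulant, and the authors themselves describe ulcers or bleeding as usual in the disease under study. The drugs used to prevent or treat those problems are then forbidden without exception. A patient with an earlier ulcer, or one already taking an indicated proton pump inhibitor, meets the eligibility criteria as written and is then barred from the drug.

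Followed literally, the rule leaves two courses: the patient stays in the trial without the drug, or leaves to get it. If the investigator treats anyway, the protocol is breached. What is at stake is mainly participant safety. The secondary cost is avoidable departures or breaches in a small trial.

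**Working it through.** The protocol gives no figure to reproduce on this point. The check is mainly a reading of the text, followed by simple counts.

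**Step 1. Does any section permit a barred drug for a participant who stays?**

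- *Intervention:* the background list is described as non-exhaustive, but the specific ban follows it and is unqualified. Reading the open list as permission would make the section contradict itself.
- *Withdrawal, Dropout, and Discontinuation:* gives a way out of the trial, not access to the drug within it.
- *Adverse Events:* promises first-aid measures and names cardiac complications. It does not lift the ban and does not address prophylaxis.
- *Randomization and Blinding:* provides for emergency unblinding and urgent measures. It does not lift the ban either.

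None does.

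**Step 2. Do the eligibility criteria remove the patients affected?** Recent antibiotic users are removed by criterion 10, so use at entry is a question about proton pump inhibitors and other gastroprotective drugs. Those users, and patients with gastric ulcer or bleeding risk, are not removed.

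**Step 3. How many are bound by the rule?** All 66, for 14 days, or up to day 14 + 3 = 17 with the visit window. At the reported trial status 20 had completed follow-up, so an amended rule can reach at most 66 − 20 = 46. These are numbers bound by the rule, not numbers in need.

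**Step 4. What would an exception cost the flora data?** Table 1 schedules stool at D1, D7 and D14.

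- Planned samples: 66 × 3 = 198 in all; 66 × 2 = 132 after baseline.
- If *k* patients start a drug after baseline, the share affected is at most 2*k*/132.

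| *k* (assumed) | Samples affected, at most | Share of 132 |
|---|---|---|
| 1 | 2 | 1.5% |
| 5 | 10 | 7.6% |
| 10 | 20 | 15.2% |
| 23 | 46 | 34.8% |
| 46 (ceiling) | 92 | 69.7% |

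- A patient on a proton pump inhibitor from entry affects all three of that patient's samples: 3/198 = 1.5%.
- Samples already collected under the present rule: at least 20 × 2 = 40, and 40/132 = 30.3% of the post-baseline total.

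The values of *k* are assumptions; the document gives no rate of use.

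**The case against.** **A journal article condenses a fuller protocol, which may hold an exception.** That is possible. But the article does not merely stay silent on rescue medication; it states a categorical rule. The point therefore holds for the text at hand and falls away if the full protocol has such a clause.

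**The investigator can decline to enrol a patient who needs a barred drug.** Participants are inpatients, and treatment history is taken at screening, so this would work in practice for known users. It does not cover a need that arises during the 14 days, and nothing in the criteria requires it.

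**Harm is not shown.** This stands. Participants are aged 40 to 60, those with a GRACE score above 140 are excluded, and treatment is short. A reader might infer from the Discussion that this regimen is known to injure the mucosa of most participants. The text does not say so: it ties mucosal damage to prolonged antiplatelet use or to several anticoagulants together, and the trial lists one anticoagulant. The sentence on ulcers or bleeding is part of a mechanistic rationale, not a rate in this population.

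**Leaving the trial costs little.** This stands in part. A reader might infer that patients who leave to get treatment are lost to the analysis, but the withdrawal section says their data are included. That answers the data question, not the clinical one.

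**The ban also protects the primary comparison.** A reader might infer that the rule serves only the flora work and has no bearing on hs-CRP. The Discussion does not support that: it hypothesises that the granule eases symptoms by improving flora disturbance and gastrointestinal injury. Drugs acting on the same pathway could affect the clinical comparison, so any exception needs an hs-CRP sensitivity analysis.

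**A loosely worded exception could admit most patients.** This also stands. With this background regimen, leaving bleeding risk to judgement alone could move use towards the 69.7% ceiling. Prophylaxis needs listed criteria.

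**Conclusion.** The point holds as a modest safety amendment. The document fixes an unqualified ban on three drug classes that some participants may need, gives no route to them for anyone who stays in the trial, and does not screen out the patients most likely to need them. A general restriction is sound; only its absolute form is at fault.

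The rule binds 66 participants, and at most 46 could still come under an amended one. The number in need is unknown, and no harm rate is claimed. The conclusion assumes that no exception exists in a fuller protocol and that the trial status is as reported. No case is made for relaxing the bans on probiotics, immunosuppressants or hormones.

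**What to change.** Keep the general restriction and add to the end of the Intervention section that a proton pump inhibitor, gastrointestinal drug or antibacterial is allowed with a documented clinical indication, namely:

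1. treatment of ulcer, bleeding or infection;
2. continuation of an indicated proton pump inhibitor taken at entry, identified from the treatment history recorded at screening;
3. prophylaxis, only under bleeding-risk criteria listed in advance, such as an earlier ulcer or gastrointestinal bleed.

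State that this overrides the separate ban on drugs acting directly on the flora, for these drugs only. Then specify:

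- drug, indication and start and stop dates go on the CRF;
- the participant stays in follow-up and in the as-randomised hs-CRP analysis;
- an hs-CRP sensitivity analysis addresses users of these drugs;
- the flora data are analysed both with and without samples taken after exposure (all three samples for a drug taken at entry);
- use is reported by arm, before and after the amendment.

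**Cost.** One amendment with ethics approval. The flora data become less clean in proportion to use: up to 1.5% of post-baseline samples per starter, or 15.2% if ten patients start. They would also come from two rules, with at least 20 participants treated under the present one. No participant leaves the hs-CRP comparison because of the exception.
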